### Sample Size Estimation

The total student population at Makerere University, Kampala, Uganda, is about 35,000 [41]. It is estimated that the sample size needed for our prevalence estimates with an expected SAD prevalence of 50% [10,12], a 95% interval, and a 2% margin of error for moderate-to-high stress, moderate-to-high anxiety, and moderate-to-high depression among Makerere University students will be 2247. A sample size calculator was used to determine the sample size [28,59,60].

Based on the previous maximum survey completion rates of 50% observed in similar programs, a minimum of 4494 students will be enrolled in the W4S email and WhatsApp messaging program over 6 months to obtain an estimated 2247 students’ completion at baseline. To achieve a power of 80% (*β*=.2) and a 2-sided significance level of 5% (*α*<.05) and to detect an effect size of 30% before and after the intervention, a sample size of 90 would be needed [49].

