### Strengths and Limitations

The strengths of this protocol include the following: first, the process of cocreation is a core strength of the intervention. This is a novel approach in low- and middle-income country eHealth interventions. This differentiates our protocol from top-down interventions and highlights participatory science.

Second, we expect that the survey will provide insightful data on the prevalence of SAD among university students. This will support the Counselling and Guidance Center of the university in tailoring interventions to the student community.

However, some limitations are anticipated. First, the outcome measures will be assessed at 1, 3, and 6 months. However, the effects of the intervention beyond 6 months remain unknown. It is also uncertain whether the benefits will decline once the daily email and WhatsApp messages end. Second, although the self-reported scales used to measure mental health variables are standardized, they are not diagnostic tools. Third, the demographics of study participants may not represent those of the wider student body at other universities (public and private or rural and urban), limiting the generalizability of the findings. Additionally, web-based surveys distributed via email and WhatsApp typically have response rates below 20%, which may hinder achieving the target sample size. Nonetheless, this will be the first study in Uganda to examine the prevalence and associated factors of SAD among students using an email and WhatsApp messaging program. We plan to use these preliminary data as a pilot for larger trials and invite collaborative follow-ups.

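### The ±2-point prevalence margin rests on a best-case 50% completion rate; at 4494 enrolled it should be stated as conditional on completion

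*Protocol article*

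**What the plan says.** The Sample Size Estimation section sizes the prevalence objective by precision. It takes a population of 35,000, an expected prevalence of 50%, and "a 95% interval, and a 2% margin of error for moderate-to-high stress, moderate-to-high anxiety, and moderate-to-high depression", and arrives at 2247 students.

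It then allows for non-completion. The reason given is "Based on the previous maximum survey completion rates of 50% observed in similar programs". Doubling 2247 on that ground yields 4494, which the section calls the least number to be enrolled, and the purpose of this figure is "to obtain an estimated 2247 students’ completion at baseline". The Methods paragraph of the Abstract gives the same 4494 as the number to be targeted.

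Under Strengths and Limitations the article adds that "web-based surveys distributed via email and WhatsApp typically have response rates below 20%, which may hinder achieving the target sample size".

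The Outcomes and Measures section uses baseline completers as the denominator for prevalence, so completion of that survey sets the precision directly. A separate requirement of 90 is given in the sample size section for the before-and-after comparison.

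**The concern.** Dividing by the highest completion rate seen in similar programs gives the smallest enrolment that could suffice. The protocol nevertheless presents the result as the estimated number of completers and recruits to it. If completion is anything less than that maximum, 4494 enrolled students do not produce 2247 completers.

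The limitations section deepens the doubt. It names the delivery mode that the Data Collection section describes for the baseline link, says response is typically below 20%, and ties this to missing the target. Nothing carries that warning back into the sample size section, where the margin stands unqualified.

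At stake is the precision of the prevalence estimates in the first objective. The correlates and the planned rural-urban analysis draw on the same completers, so they would lose precision too.

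**Working it through.** **Inputs (Sample Size Estimation).** Population N = 35,000; prevalence p = 0.50; 95% confidence, z = 1.96; margin d = 0.02; completion rate 0.50.

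**Step 1: reproduce the plan's figures.**

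- Without finite population correction: n0 = z²p(1−p)/d² = 1.96² × 0.25 / 0.02² = 2401.
- With correction: n = n0/(1 + (n0 − 1)/N) = 2401/(1 + 2400/35,000) = 2246.9, rounded up to 2247.
- Enrolment: 2247/0.50 = 4494.

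Both figures reproduce, so there is no arithmetic error.

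**Step 2: margin delivered by 4494 enrolled at other completion rates.** Margin = 1.96 × √(0.25/n) × √((N − n)/(N − 1)), with n = 4494 × completion rate. The last column is 2247 divided by the completion rate.

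| Completion among enrolled | Completers | Margin (points) | Enrolment needed for 2247 |
|---|---|---|---|
| 50% | 2247 | ±2.0 | 4494 |
| 40% | about 1798 | ±2.25 | 5618 |
| 30% | about 1348 | ±2.6 | 7490 |
| 20% | about 899 | ±3.2 | 11,235 |
| 10% | about 449 | ±4.6 | 22,470 |

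Worked line for 20%: 1.96 × √(0.25/899) = 3.27 points; times √(34,101/34,999) = 3.23 points, about 1.6 times the stated margin. The 11,235 in that row is 32% of 35,000.

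**Step 3: what the below-20% figure could refer to.**

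- *Subscribers.* It then competes with the 50%, and the rows at 20% and lower apply.
- *Everyone invited.* If all 35,000 are invited (an assumption), 4494 enrolled is 4494/35,000 = 12.8% and 2247 completers is 2247/35,000 = 6.4%. Both lie below 20%, so the two statements can hold together. The warning then bears on recruitment: 10% response would give 3500 enrolled and, at 50% completion, 1750 completers and ±2.28 points.

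**Step 4: does the document settle it?** It does not, because the order of steps differs by section.

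- *Study Design* places the baseline survey before recruitment, then says those who subscribe receive its link.
- *Data Collection* sends the link to students and offers subscription after baseline.
- *Participants' Recruitment and Subscription* has subscription and consent first, then the baseline link.

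If baseline comes before subscription, a completion rate among enrolled students does not describe the baseline survey at all.

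**The case against.** The strongest objection is that the two rates measure different things. The 50% is completion among students who have already enrolled, and the below-20% figure is a response rate for distributed surveys. Outcomes and Measures lists uptake, response and completion as separate proportions, and the arithmetic for invitees above shows that the figures are compatible. This stands. A reader might infer that the protocol contradicts itself, or that it forecasts about 899 completers and ±3.2 points. The text supports neither: the limitations sentence is a general caution about such surveys, and its denominator is not given.

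Three further points have some force.

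- **4494 is called a minimum.** Nothing caps enrolment there, and the app reports subscriber and completion counts as they accrue. But no rule extends enrolment if completion is low, and the Abstract treats 4494 as the target.
- **The risk is disclosed.** That is so, but its effect on the stated margin is not.
- **p = 0.50 is the widest case.** At the 22% depression prevalence that the Introduction cites for Makerere medical students, 899 completers give 1.96 × √(0.22 × 0.78/899) = 2.7 points. The plan's own calculation, however, uses 50% for all three conditions.

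None of these removes the central point, which does not need the 20% figure: a maximum has been used as the planning value.

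**Conclusion.** The concern holds as one of an optimistic assumption, not of arithmetic and not of a proven contradiction. At the plan's own p = 0.50 and N = 35,000, the ±2-point margin is the best case for 4494 enrolled students. Any completion rate below 50% misses it, modestly at 40% (±2.25) and more clearly at 20% (±3.2) or 10% (±4.6).

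The size of any shortfall cannot be fixed from the document, because the expected completion rate among subscribers is not given apart from its maximum. For that reason ±3.2 should not replace ±2 as the planning precision. Since the limitations text says below 20%, 899 would not be a lower bound either, even if that rate applied to subscribers.

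The consequence is limited to the precision of the prevalence objective and of analyses that draw on the same completers. The pre-post requirement of 90 would still be met at baseline with about 449 completers. This is something that should be fixed, not a fault that undermines the study.

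**What to change.** Keep 4494 and change the wording of the Sample Size Estimation section.

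1. State that ±2 points is the best case, reached if half of the enrolled students complete the baseline survey, and give the margin by completion rate: 50%, 2247 completers, ±2.0; 40%, about 1798, ±2.25; 30%, about 1348, ±2.6; 20%, about 899, ±3.2; 10%, about 449, ±4.6 (p = 0.50, N = 35,000).
2. Define the denominator of the 50% rate there, and of the below-20% rate under Strengths and Limitations: invited, subscribed or sent a link.
3. Reconcile the order of baseline survey and subscription across Study Design, Data Collection, and Participants' Recruitment and Subscription, so that it is clear to whom the completion rate applies.

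The Abstract quotes no margin and needs no edit on this point. Enrolment and conduct need not change. The cost is a less favourable statement of precision.

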### Statistical Analysis

Once data are downloaded from the W4S server, the data from the baseline and follow-up surveys will be exported to STATA version 17 for data analysis. Observations with more than 50% missing responses will be omitted from the dataset. Otherwise, missing data on individual variables will be handled using multiple imputation with baseline and postbaseline variables [61].

At baseline, frequency distributions will be used to summarize categorical variables, while means and SDs will be used for continuous variables. Chi-square tests and/or *F* statistics will be used to measure the association between demographic characteristics and SAD variables. Multivariable logistic regressions will be used to determine the correlates of SAD among MAK undergraduate students. We plan to conduct rural-urban disaggregated analysis to account for diversity among the students.

Paired sample 2-tailed *t* tests and proportion tests will be used to assess significant differences in mean scores and prevalence rates of SAD at baseline, 1 month, 3 months, and 6 months. Profile plots of mean scores will be generated while controlling for background characteristics. All findings will be reported at 95% CI with a significance level of 5% (*P*<.05). The data will be analyzed using Stata version 17.

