### Specific Objectives

This study has the following objectives: (1) to determine the prevalence and correlates of SAD among university students in Uganda, (2) to investigate the effectiveness of the daily W4S supportive messages in reducing levels of SAD and in improving well-being among university students in Uganda, and (3) to investigate the participants’ experience and satisfaction associated with the W4S daily SMS text messaging support.

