### Data Collection

An online baseline survey will be conducted to assess the mental health of the students.

A link to the baseline survey will be sent to the students through their email and WhatsApp. Clicking on the link to the baseline survey will indicate consent required for participation in the survey. The data collection portal is secure and password-protected with dual authentication, which minimizes data breaches. In addition to the demographic questions, participants will fill out the online screening tools for assessing SAD and well-being. It is on this basis that they will be diagnosed (to have or not to have) with at least one of the 3 outcomes [8,48-50]. The app is programmed to produce summaries of the total number of subscribers at any given point in time and how many have completed the different phases.

All participants will be able to view their scores for each mental health outcome (SAD). Depending on the severity of the mental health scores, recommendations will be provided to participants. All students, whether diagnosed with SAD or not, will have the option to enroll in the W4S program and will be made available through a postbaseline subscription link. The baseline survey and intervention enrollment will be conducted from March 2026 to cover the second semester of the academic year 2025/2026 at Makerere University.

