### Outcomes and Measures

Primary outcome measures at baseline, 1 month, 3 months, and 6 months will be the mean difference in scores on the PSS-10, GAD-7 scale, and PHQ-9 [49,56-58]. Prevalence estimates for SAD will be calculated as the total number of undergraduate students assessed as likely to have a particular condition divided by the total number of students who completed the baseline survey. In addition, proportions for survey uptake, response rates, and completion rates will be calculated. Finally, the outcomes related to the feasibility or acceptance of the tool, along with measures of engagement and adherence, will be collected at the end of the follow-up survey.

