### Hypotheses

We hypothesize that the W4S email and WhatsApp messaging program will reduce the prevalence and severity of SAD among Makerere University students. We also hypothesize that the prevalence of moderate-to-high stress, moderate-to-high anxiety, and moderate-to-high depression would be comparable to the prevalence of these conditions reported among university students in East Africa (Kenya and Tanzania) and in other jurisdictions. Finally, we hypothesize that demographic factors, socioeconomic factors, organizational factors, and class size will be associated with SAD among students.

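### The only adjusted model named for the correlates of SAD is logistic regression on moderate-to-high status; adding regressions of the full scores would recover information at almost no cost

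*Protocol article*

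**What the plan says.** Specific Objectives gives the first objective as "to determine the prevalence and correlates of SAD among university students in Uganda". The Hypotheses section adds that "demographic factors, socioeconomic factors, organizational factors, and class size will be associated with SAD among students".

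Statistical Analysis sets out two steps for this at baseline. The bivariate step is "Chi-square tests and/or *F* statistics will be used to measure the association between demographic characteristics and SAD variables". The adjusted step is "Multivariable logistic regressions will be used to determine the correlates of SAD among MAK undergraduate students". A subgroup analysis follows: "We plan to conduct rural-urban disaggregated analysis to account for diversity among the students".

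The logistic model needs a yes/no outcome. Data Collection derives one from the screening scales: "It is on this basis that they will be diagnosed (to have or not to have) with at least one of the 3 outcomes". Sample Size Estimation describes the states as moderate-to-high stress, anxiety and depression, and plans on an "expected SAD prevalence of 50% [10,12], a 95% interval, and a 2% margin of error".

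Outcomes and Measures, by contrast, keeps the same scales as scores. The primary outcome is "the mean difference in scores on the PSS-10, GAD-7 scale, and PHQ-9".

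**The concern.** A cut-off is needed to state a prevalence. It is not needed to test which factors go with stress, anxiety or depression. Once a score is cut, a student just below the threshold counts the same as one with no symptoms, and a student just above it the same as one with severe symptoms. The differences within each group no longer contribute to the estimate.

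The baseline sample is sized for the precision of a prevalence, and no power is stated for the correlates. The abstract's conclusions promise to identify the students most at risk, and the adjusted models are where independent correlates would be found. If those models use only the cut, weaker or less common correlates are more likely to be missed or imprecisely estimated, above all within the rural and urban groups. The full scores will already be in the dataset.

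**Working it through.** **1. The plan's own sample size.** Inputs from Sample Size Estimation: p = 0.50, margin 0.02, 95% interval, population 35,000, completion 50%.

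- n0 = 1.96² × 0.25 / 0.02² = 2400.9.
- Finite population correction: 2400.9 / (1 + 2399.9/35,000) = 2246.8, so 2247.
- 2247 / 0.50 = 4494.

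Both stated figures reproduce. The 80% power in the same section belongs to the before-after comparison (N = 90), not to the correlates.

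**2. Information kept after the cut.** For a normal score and a covariate that shifts its mean, the efficiency of the dichotomised analysis relative to the full-score analysis is φ(z_p)² / [p(1 − p)]. Here p is the share above the cut, z_p the matching normal quantile and φ the standard normal density.

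- p = 0.50 (the planning value): 0.3989² / 0.25 = 0.637. About 36% of the information is lost, and 2247 × 0.637 ≈ 1430.
- p = 0.22 (depression among medical students at the same university, cited in the Background): 0.2961² / 0.1716 = 0.511. About 49% is lost, and 2247 × 0.511 ≈ 1148.

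**3. What that means for power.** For a characteristic held by a share q of students and a difference of d SD, two-sided 5%: power = Φ(d × √[N q(1 − q) × E] − 1.96). E is 1 for the score and 0.637 or 0.511 for the cut. The values of d and q are assumptions.

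| N | q | d (SD) | Score | Cut at 50% | Cut at 22% |
|---|---|---|---|---|---|
| 2247 | 0.50 | 0.118 | 80% | 61% | 52% |
| 2247 | 0.50 | 0.20 | 99.7% | 96.6% | 92.3% |
| 2247 | 0.50 | 0.30 | >99.9% | >99.9% | 99.9% |
| 2247 | 0.10 | 0.20 | 81% | 62% | 53% |
| 899 | 0.50 | 0.20 | 85% | 67% | 57% |

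Worked example for the fourth row: 0.20 × √(2247 × 0.09) = 2.844.

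- Score: Φ(2.844 − 1.96) = 0.81.
- Cut at 50%: Φ(2.844 × √0.637 − 1.96) = 0.62.
- Cut at 22%: Φ(2.844 × √0.511 − 1.96) = 0.53.

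The last row uses 20% of 4494 = 899, a pessimistic reading of the response rate given in Strengths and Limitations.

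**4. Check on the approximation.** A simulation of the fourth row (20,000 runs, two groups, Wald test of the log odds ratio) gave 81% for the score and 61% for the cut at 50%. For the cut at 22% it gave 57% if the 10% group scores higher and 48% if it scores lower. The formula's 53% lies between these.

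**5. Smallest detectable difference.** At 80% power with 2247 completers and an even split, it is 2.802 / √(2247 × 0.25) = 0.118 SD on the score. On the cut it is 0.118/√0.637 = 0.148 SD or 0.118/√0.511 = 0.165 SD.

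**The case against.** **The logistic model fits the stated question.** Objective 1 pairs prevalence with correlates, Data Collection classes students as having or not having each condition, and the second hypothesis concerns moderate-to-high states. Which students are likely to be cases is a binary question, while a linear model estimates a shift in the mean score, which is a different quantity. This stands. It is why the logistic models should remain, and why this is a matter of efficiency and not an error or contradiction.

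**The plan is not confined to cut scores.** A reader might infer that correlates are sought only on dichotomised data. The text does not support that, because an F statistic can compare mean scores across groups. What remains is that those tests are unadjusted. The profile plots of mean scores controlling for background characteristics are described with the follow-up comparisons and are not a model of correlates.

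**The large power loss is conditional.** A reader might also take 19 to 28 points as the cost for this study. It is the cost only where the full-score analysis has about 80% power, and the documents give no correlate effect size that would put the study there. With an even split at the planned size, differences of 0.20 SD or more lose about 7 points or fewer.

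**The inputs are soft.** The 22% refers to depression in medical students and need not apply to stress or anxiety. The general response rate below 20% is not the 50% completion that the plan assumes for enrolled students. The scores may be skewed. No rural or urban group sizes are given, so the loss within that split cannot be computed. All of this limits the size of the claim but leaves its direction unchanged.

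**A condensed article may leave further models to an analysis plan.** That is possible, and nothing in the article excludes them. The point concerns the one adjusted model that the article does name.

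**Conclusion.** The point holds as a worthwhile, low-cost improvement. The sole adjusted model named for the correlates uses a cut outcome, although the scores are collected and serve as continuous measures for the primary outcome. Under a roughly normal score and a mean-shift effect, the cut keeps about 64% of the information at 50% prevalence and 51% at 22%.

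In power terms the cost is minor for common characteristics with moderate effects: 3 to 7 points at 0.20 SD, and under 1 point at 0.30 SD. It is substantial, about 18 to 28 points in the cases worked, for effects near 0.12 SD, for a characteristic held by 10% of students at 0.20 SD, or if only about 900 students respond. All effect sizes and covariate shares are assumptions. The documents do not support calling the logistic analysis wrong or replacing it.

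**What to change.** In Statistical Analysis, after the sentence on logistic regression, add a prespecified multivariable regression of each baseline score (PSS-10, GAD-7, PHQ-9) on the same covariates. Use a linear model with robust standard errors, or a proportional-odds model if the scores are skewed. Apply it in the rural-urban analysis as well. State that these models test which factors are associated with stress, anxiety and depression, and that they are reported beside the logistic models, which give the odds ratios of moderate-to-high status.

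The cost is one extra model per scale on data already collected, and one or two sentences of text. The downside is that a mean score difference is less familiar to policy readers than an odds ratio, but the odds ratios will still be reported.

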## Methods

### Study Design

The study used a quantitative longitudinal study design. It will be implemented in three phases: (1) the cocreation and adaptation of the intervention; (2) the baseline survey; and (3) follow-up surveys conducted at 1 month, mid-term follow-up at 3 months, and an endline at 6 months. The cocreation phase was completed during the recess term (July 2025). The next 2 phases, baseline and follow-ups, will be implemented between February 2026 and October 2026. Recruitment will begin in February 2026 and will last for 3 months up to April 2026. There will be an observation period of 6 months for the enrolled participants [28,33,43].

The email and WhatsApp messaging intervention was cocreated and adapted by the study team together with purposively selected students and identified stakeholders. Thereafter, a baseline survey will be conducted before recruitment to estimate the prevalence of SAD. Students at Makerere University will be invited via email and WhatsApp to self-subscribe to the W4S program. All participants who subscribe to the intervention will receive a link to the online baseline survey, daily supportive messages for 6 months, and the follow-up survey links at 1-, 3-, and 6-month postenrollment time points [33,43].

The rationale for the nonrandomized design is based on resource constraints. We have funding to implement a pilot survey and use the preliminary results to apply for a bigger grant to implement a fully randomized controlled trial.

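### Change in SAD prevalence within the same students is assigned to proportion tests of unstated type; the usual two-sample version would give conservative P values and over-wide confidence intervals

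*Protocol article*

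**What the plan says.** The Statistical Analysis section covers both kinds of outcome in one sentence: "Paired sample 2-tailed *t* tests and proportion tests will be used to assess significant differences in mean scores and prevalence rates of SAD" at baseline and at the three follow-ups. Means are matched with t tests and prevalence with proportion tests. The part that bears on prevalence runs: "proportion tests will be used to assess significant differences in mean scores and prevalence rates of SAD at baseline, 1 month, 3 months, and 6" (the last in months). The type of proportion test is not given, and no paired binary method appears elsewhere in the article.

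The data are repeated measurements on one cohort without a control group. Under Study Design, each subscriber receives the baseline survey link, "daily supportive messages for 6 months, and the follow-up survey links at 1-, 3-, and 6-month postenrollment time points".

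The primary outcome is continuous: under Outcomes and Measures it "will be the mean difference in scores on the PSS-10, GAD-7 scale, and PHQ-9". Change in prevalence is nevertheless in the abstract's objective and the study aims, and the Hypotheses section states that the program "will reduce the prevalence and severity of SAD among Makerere University students".

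**The concern.** In ordinary usage a proportion test is either a one-sample test or a comparison of two independent samples. The two-sample version takes the variance of the difference as the sum of two binomial variances, with no covariance term. That describes two unrelated groups of students. Here a student who is a case at baseline is more likely than others to be a case later, so the covariance is positive and the two-sample standard error is too large.

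Prevalence and severity are the two halves of one effectiveness hypothesis. If severity is judged by a paired test and prevalence by an unpaired one, a report that scores fell but prevalence did not could come from the choice of test alone.

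**Working it through.** **The plan's own figures.** Sample Size Estimation says that "to detect an effect size of 30% before and after the intervention, a sample size of 90 would be needed", with 80% power and a two-sided 5% level. Reading 30% as a standardised paired difference of 0.30:
- normal approximation: (1.96 + 0.8416)² / 0.30² = 87.2, so 88;
- noncentral t: 90 pairs (power 80.4%; 89 pairs give 79.9%).

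So 90 reproduces as a paired t test. A two-sample design would need 175 per group.

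The prevalence-precision figure also reproduces: 1.96² × 0.25 / 0.02² = 2401; 2401 / (1 + 2400/35,000) = 2247; 2247 / 0.5 = 4494. Neither 90 nor 2247 rests on the test of prevalence change.

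**Inputs for the check.** From the protocol: baseline prevalence 50%, two-sided 5% level, 2247 baseline completers, 90 for the before/after comparison. Assumed, because the documents give no value: phi, the correlation between a student's case status at baseline and at follow-up, taken as 0.3 to 0.5.

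**Formulas, n complete pairs.**
- Two-sample variance: [p0(1−p0) + p1(1−p1)] / n.
- Correct variance: the same minus 2·phi·√[p0(1−p0)p1(1−p1)] / n. For p0 close to p1 this is the two-sample variance times (1 − phi).
- SE inflation: 1/√(1 − phi).
- True type I error of the nominal 5% test: 2[1 − Φ(1.96/√(1 − phi))].

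| phi | SE and CI width too large by | True type I error | Coverage of nominal 95% CI |
|---|---|---|---|
| 0 | 0% | 5.0% | 95.0% |
| 0.3 | 20% | 1.9% | 98.1% |
| 0.5 | 41% | 0.6% | 99.4% |

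**Power for a small effect, 50% to 47%, 2247 complete pairs.** The two-sample SE is √[(0.25 + 0.2491)/2247] = 0.01490. The correct SE is 0.01247 at phi 0.3 and 0.01054 at phi 0.5.
- Two-sample test: Φ[(0.03 − 1.96 × 0.01490)/0.01247] = Φ(0.06), about 53%; at phi 0.5 also about 53%.
- McNemar: Φ(0.03/0.01247 − 1.96) = Φ(0.45), about 67%; at phi 0.5, Φ(0.89), about 81%.

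Simulation with 200,000 replicates agrees, with McNemar's type I error at 5.0%.

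**Power with few pairs, 50% to 35%, 90 pairs (simulation).** Two-sample 54%; McNemar 69% (phi 0.3) and 84% (phi 0.5).

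**Power at the plan's own effect of 0.30.** Here the scores are treated as bivariate normal with correlation r = 0.5 to 0.7, cut to give 30% or 50% baseline prevalence (phi about 0.3 to 0.5).
- 2247 pairs: both tests about 100%.
- 899 pairs: loss of about 1 point or less.
- 449 pairs: loss of about 2 to 14 points.
- 90 pairs: loss of about 13 to 24 points.

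**Partial overlap.** Suppose all 2247 baseline completers are compared with m = 449 of them at follow-up. This is 20% of 2247, an illustration suggested by the response rates below 20% mentioned under Strengths and Limitations. The SE inflation becomes 1/√[1 − 2m·phi/(2247 + m)] = 1/√(1 − 0.333·phi), which is 1.05 at phi 0.3 and 1.10 at phi 0.5.

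**The case against.** The strongest reply is that the protocol never says independent samples. The words paired sample open the sentence and can be read as governing both tests, and McNemar's test is the paired comparison of two proportions. The 90 in Sample Size Estimation is a paired figure, so the authors were thinking in pairs. A condensed article may also leave the exact variant of a test to a fuller document.

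Much of this stands. A reader might infer that the planned P values and intervals for prevalence are simply wrong. The text does not support that, because the fault depends on a choice it leaves open. A reader might also infer that real reductions will generally be missed. That does not follow either: at the plan's own effect with many pairs the loss is trivial, and it becomes large only for small effects, few pairs or high correlation. Nor could the error produce a false claim of effectiveness, since with positive correlation it is conservative.

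What remains is that the article names a test for a stated hypothesis. In ordinary usage that name points to an unpaired test, and an analyst could not tell from the sentence what to run. Naming the method is a better choice of test rather than a request for detail.

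**Conclusion.** The point holds as a conditional one. Only the t test is unambiguously paired. If the usual two-sample proportion test is applied to the same students, its P values and 95% intervals for change in prevalence will be conservative: intervals about 20% to 41% too wide and true type I error about 1.9% to 0.6% for phi of 0.3 to 0.5 with complete pairs. The loss of power runs from negligible to substantial, with the fall from 50% to 47% in 2247 pairs (53% against 67% to 81%) at the substantial end.

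These sizes rest on an assumed phi; at phi = 0 nothing is lost, and partial overlap through dropout shrinks the effect. The primary mean-score analysis and the figures of 90, 2247 and 4494 are untouched. The change is worth making because lower prevalence is a stated objective, aim and hypothesis.

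**What to change.** In Statistical Analysis, replace proportion tests with one of the following:
- McNemar's test, with the paired difference in prevalence and its 95% CI (Stata mcc), for each of stress, anxiety and depression at each follow-up against baseline; or
- one GEE or mixed-effects logistic model per condition, with time as a factor and clustering on student.

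McNemar's test uses complete pairs only, while the model also uses students who miss some waves. That favours the model if dropout is heavy.

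The cost is one sentence and a different Stata command. Records must be linked by student, which the planned paired t tests already require. No extra data or participants are needed.
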